### Pre-established criteria

Feasibility of conducting a larger-scale evaluation will be interpreted based on the following:
The recruitment goal has been reached (66 participants in 10 months).Behaviour change data are collected for ≥ 75% of participants recruited within the study.Physical functioning data (collected on a subset of participants) can be collected for ≥ 75% of participants that (a) reside within 30 km from a study testing site and (b) are invited to complete testing.

The success of the intervention will be interpreted based on the following:
The acceptability of the intervention is satisfactory (score of ≥ 20 on the client satisfaction questionnaire) [34].The system usability is satisfactory (score of ≥ 68 on the software usability scale) [35].There is no grade 3+/life threatening or severe adverse events attributed to participating in the intervention using the Common Terminology Criteria for Adverse Events V.5.0 grading criteria.There is evidence of meaningful participation in either aerobic activity and or resistance-based activity in the intervention group relative to the wait-list control. As the exercise prescription will be personalised, it is difficult to specify an average cut-point; however, we anticipate a between-group difference of at least 30 min of aerobic activity and/or one session of resistance training. This would be indicative of behaviour change that is in line with the minimum level of exercise progression prescribed in our intervention and should also allow us to detect differences in maintenance of activity (equivalent to one session per week) amongst those that enter the study already completing some exercise.

The trial team will determine if progression to a larger scale evaluation is warranted based on the criteria and will work together to revise aspects of the protocol if problem areas are identified (e.g. if recruitment is slow the study may still progress if additional recruitment sites can be secured). The process evaluation will be used to inform improvements to the intervention if usability, acceptability or potential for efficacy issues are identified.

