### Randomisation

Once baseline data have been collected, participants will be randomised into the intervention group or the control group at a ratio of 1:1. The study statistician (AV) will produce the random computer-generated number sequence in random block sizes of length 2 and 4, and will be blinded to identifying information. Stratification will occur based on age (≤ 65 years, > 65 years of age) and differences in physical function as determined by the EORTC QLC-30 (≤ 80, > 80). This is to control for potential confounders relating to age (including confidence using technology) and physical capacity. Participants will not be blinded to the primary goal of the project (evaluation of web-based tool in this population) but will not be informed of the pre-specified criteria for success.

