### Data analysis

#### Sample size

As this is a pilot study, which uses pre-specified criteria for success rather than a primary outcome, a formal sample size calculation was not essential [69]. Similar 2-arm pilot studies have reported sample sizes of 36 and 30 per arm for dichotomous and continuous endpoints, respectfully [70]. Similar to these studies, the enrolment target for this trial is 66 participants, 33 in each arm. Using a sample size calculation method created for pilot studies by Vichtbauer al., it was determined that the above sample size will allow us to identify feasibility problems (drop out, safety issues etc.) with a reasonable probability of occurring (i.e. a probability of 10% or greater), with a 95% level of confidence [71]. If issues are detected the trial team will review and consider if progression to a larger trial is warranted and feasible.

Study data will be analysed using SPSS version 26 (IBM, Chicago, IL, USA). Descriptive statistics will be calculated for all study variables. ANCOVAs (or non-parametric equivalents) will be used to conduct between-group comparisons, with potential confounders included in the model (e.g. age, time since diagnosis, treatment status and baseline outcome assessments). Treatment effects will be estimated as covariate-adjusted mean differences between the two treatment groups at follow up. A senior University of Adelaide statistician employed by the Freemasons Foundation Centre for Men’s Health will oversee the analyses. Sensitivity analyses will be conducted to explore the impact of missing data and remove any individuals who were unable to be prescribed with exercise from the analysis.

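### The covariates named for the ANCOVA leave out physical function, one of the two stratification factors, and a non-parametric fallback may not give the difference that the 30-minute criterion is set against

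*Protocol article*

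**What the plan says.** Four places in the protocol article bear on this point.

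- **Randomisation.** "Stratification will occur based on age", cut at 65 years, and on "differences in physical function as determined by the EORTC QLC-30", cut at 80. The reason given is: "This is to control for potential confounders relating to age (including confidence using technology) and physical capacity".
- **Data analysis (paragraph under Sample size), method.** "ANCOVAs (or non-parametric equivalents) will be used to conduct between-group comparisons". The covariates are then given by example: "with potential confounders included in the model (e.g. age, time since diagnosis, treatment status and baseline outcome assessments").
- **The same paragraph, effect measure.** "Treatment effects will be estimated as covariate-adjusted mean differences between the two treatment groups at follow up". No exception is made for the non-parametric case.
- **Pre-established criteria.** For behaviour change in the intervention arm relative to the wait-list arm, "we anticipate a between-group difference of at least 30 min of aerobic activity and/or one session of resistance training".

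The planned size is small: "the enrolment target for this trial is 66 participants, 33 in each arm".

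**The concern.** The Randomisation section treats age and physical capacity as the two potential confounders worth building into the design. The analysis paragraph uses the same term for its covariates, names age, adds two variables that were not stratified on, and does not name physical function. Stratifying on a prognostic variable makes the arms more alike than chance alone would. An analysis that leaves the variable out still counts its variation as noise, so the reported standard error is too large for the design that was run.

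The second issue is the effect measure. Weekly minutes and session counts are bounded at zero and plausibly skewed, so they are the outcomes most likely to prompt a non-parametric method. The next sentence of the plan promises a covariate-adjusted mean difference, and a rank procedure estimates something else.

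At stake is the between-group behaviour difference, one of four criteria for the success of the intervention that inform progression to a larger trial. An unnecessarily wide interval, or a shift on a different scale from the mean, blurs the comparison with 30 min or one session.

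**Working it through.** **The plan's own figure.** The only computed figure is the problem-detection sample size. n = ln(1 − 0.95)/ln(1 − 0.10) = 28.4, so 29 are needed. With 33 per arm, the chance of seeing at least one occurrence is 1 − 0.9^33 = 96.9%. The stated size holds, and nothing below changes it.

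**Stratification factors against named covariates.**

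| Variable | Stratified on | Named as covariate |
|---|---|---|
| Age | yes | yes |
| EORTC physical function | yes | no |
| Time since diagnosis | no | yes |
| Treatment status | no | yes |
| Baseline outcome assessments | – | yes |

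The last row covers physical function when physical function is itself the outcome. For minutes or sessions it naturally means baseline minutes or sessions.

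**Effect on the standard error.** Let r be the correlation between physical function and the outcome that remains after the other covariates. The document gives no value, so 0.2 to 0.4 is assumed. The standard error without the variable, relative to that with it, is 1/√(1 − r²):

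- r = 0.2: 1/√0.96 = 1.02. The interval is as wide as one from 66 × 0.96 = 63.4 participants, about 3 fewer.
- r = 0.4: 1/√0.84 = 1.09. The interval is as wide as one from 66 × 0.84 = 55.4 participants, about 11 fewer.

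**Check by simulation.** The set-up was 66 participants, four strata, random blocks of 2 and 4, 2,000 runs per scenario, two-sided 5% tests, and an assumed baseline–outcome correlation of 0.5.

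| Stratum–outcome correlation | Type I error, stratum out | Type I error, stratum in | Mean SE out / in |
|---|---|---|---|
| 0 | 4.0% | 4.1% | 0.2138 / 0.2139 = 1.00 |
| 0.3 | 2.9% | 4.0% | 0.2138 / 0.2004 = 1.07 |
| 0.5 | 1.8% | 5.3% | 0.2139 / 0.1746 = 1.225 |

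The simulation error on a 5% rate is √(0.05 × 0.95/2000) ≈ 0.5 percentage points, so differences of a point or less should not be read closely. The formula agrees. A stratum–outcome correlation of 0.3 gives a residual r² of 0.09/(1 − 0.25) = 0.12, and 1/√0.88 = 1.07. A correlation of 0.5 gives r² = 0.25/0.75 = 0.333, and 1/√0.667 = 1.225. These two scenarios have residual correlations of about 0.35 and 0.58, so the last lies above the 0.2 to 0.4 range.

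**Mean difference against a rank-based shift.** Control minutes were assumed log-normal with mean 100 and SD 120, and the true mean difference was set at about 30 min. The Hodges–Lehmann shift was then:

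- every participant gains 30 min: about 29 min (30 apart from sampling error);
- a quarter of participants gain 120 min: about 23 min;
- a 1.3-fold change in everyone: about 17 min.

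The same mean benefit can therefore fall well short of 30 on the rank-based scale.

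**The case against.** The strongest reply is that the covariates are given as examples. Such a list excludes nothing, and because the Randomisation section itself calls physical capacity a potential confounder, the model may well include it. A broad reading of baseline outcome assessments could also bring it in, since the EORTC questionnaire is a health outcome. This stands to the extent that the document does not exclude physical function. It remains true that the document does not commit to it either.

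Three stronger readings are tempting and are not supported.

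- **That covariates will be picked after seeing the data.** Reporting the smallest p-value over all subsets of five candidate covariates would raise type I error to about 8% to 11% in the same simulation. Nothing says this will be done. Closing the list and setting the rule for switching methods are ordinary tasks of a statistical analysis plan, which is not shown.
- **That the 30-minute criterion becomes impossible to compute.** The plan commits to adjusted mean differences without exception and promises descriptive statistics for all variables. The criterion states an anticipated difference and requires no test. A rank method can also give a shift in minutes.
- **That the omission biases the result.** It does not; the error is in the conservative direction.

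It is also fair to say that physical activity is a secondary exploratory outcome in a pilot without a formal power calculation, and that progression is decided by the trial team's judgement.

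**Conclusion.** The point holds in a limited form. A model built from the covariates as named leaves out one of two stratification factors for the activity outcomes. The consequence is conservative tests and wider intervals: a standard error about 2% to 9% larger for a residual correlation of 0.2 to 0.4, and no loss if physical function is unrelated to the outcome. The correlations are assumptions.

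The wording that allows non-parametric equivalents does not fit the adjusted mean difference promised in the next sentence. Under skew, a rank-based shift may fall on the other side of 30 min from the mean difference. How far depends on the assumed distribution and on how the benefit is spread across participants. Neither issue threatens the feasibility aims. Both touch one success criterion and can be settled by wording.

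**What to change.** Add baseline EORTC physical function to the named ANCOVA covariates, beside age and the baseline value of the outcome. Time since diagnosis and treatment status can stay if the sponsor wishes; nothing here argues for dropping them.

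State that, for the behaviour criterion, the covariate-adjusted mean difference in minutes or sessions is reported in all cases with its 95% interval. Where the outcome is skewed, keep the same model and use robust or bootstrap intervals. Any rank test is supplementary.

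The cost is one degree of freedom and a few lines of text. Physical function is needed for stratification and is therefore already collected before randomisation, so no new data are required and the sample size does not change.

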#### Qualitative analysis

Any verbal feedback from participants will be recorded (with permission) and transcribed verbatim. A thematic assessment will be undertaken to analyse the data as completed by Braun and Clarke [72]. This approach is data-driven and involves becoming familiar with the data, generating initial codes, searching for themes amongst codes and refining the themes to fit the data better.

### Protocol changes

Future amendments to the protocol will be considered and approved by the Steering Committee and resubmitted for ethical approval. Approved amendments will be subsequently distributed to participants through the study website.

## Discussion

The primary objective of the trial is to assess key areas of uncertainty regarding the use of ExerciseGuide (and other similar programmes) in future practice and research, including issues relating to feasibility, safety and potential for efficacy. Publication of this protocol aims to ensure transparency around pre-specified criterion for success, aid replication of study and intervention methods, and inform interested parties of the upcoming trial results.

ExerciseGuide represents a novel approach to providing more geographically accessible individualised exercise prescription with distance-based multidisciplinary support. The addition of distance-based supervision, tailored behavioural change strategies and telehealth support, may improve adherence to distance-based interventions, which are currently seen as inferior in comparison to the gold standard ‘face-to-face’ intervention [23, 29]. Increasing the feeling of personalisation, connectedness, and support through eHealth has been one method to address the disparity between the two approaches. It is anticipated that an intervention of this type would not replace face-to-face interventions, but rather play a role alongside on-site interventions as an alternative where no onsite interventions can be made available due to staffing or financial shortages.

Despite the potential advantages, there are a number of implementation issues that may be encountered when delivering a programme like ExerciseGuide. These need to be mitigated in order for high-quality implementation and evaluation to occur in the future. For example, whilst the use of eHealth technologies is useful to increase accessibility to individuals in remote areas, it is important to note that internet connection and reliability are reduced in remote Australian areas [73]. Our provision of both written (printable) and video-based exercise prescription and education may improve access to those with poor Internet connections; however, those without a connection will remain without accessible support. Adherence to health behavioural change and exercise interventions is another limitation noted in the eHealth literature [26]. We have attempted to improve adherence by working with consumers to refine content and by undergoing iterative usability testing in order to improve the user experience. We have also included elements of human support which should further enhance engagement. Lastly, it is well known that recruiting older males into health interventions is difficult [74]. Numerous different recruitment strategies will be included such as mass mailing via prostate cancer registries, health service referrals and community outreach. Further to this, advertising materials were gender-specific and mass mailouts through the prostate cancer registry were personalised. Data from this trial will provide useful information regarding the success of these mitigation strategies.

Pilot trials studies of this nature can possibly reduce research waste and more significantly, they can lead to changes in development and design in order to maximise the intervention and trial characteristics for future trials [75]. Usability, acceptability, adverse events, safety, and evidence of aerobic activity or resistance-based activity participation will all be monitored to determine if progression to a full randomised control trial is worthwhile.

## Data Availability

Not applicable.

## Abbreviations

SPIRIT: Standard Protocol Items: Recommendations for Interventional Trials
CTCAE: Common Terminology Criteria for Adverse Events
EORTC QLC-30: European Organisation for the Research and Treatment of Cancer Quality of Life Questionnaire-30 items
WB: Weight bearing
NWB: Non-weight bearing
EP: Exercise physiologist
